# SUMMARY

| **Title** | Effectiveness of a Short, Intensive and Standardised Spa Therapy for Subacute and Chronic Low Back Pain on Return to Work for Patients in Sick Leave From 4 to 24 Weeks Duration |
| --- | --- |
| **Principal Investigator** | [name] (Hôpital Cochin) |
| **Recruiting sites** | Hôpital Cochin AP-HP Paris, Hôpital Nord CHU Clermont-Ferrand, Hôpital Lapeyronie CHU Montpellier, CHU Nancy, Etablissements thermaux d’Aix les Bains et Dax |
| **Spa centres** | Saint Amand les eaux, Royat, Balaruc les Bains, Amnéville les Thermes, Aix les bains et Dax. |
| **Study duration** | 36 months (24-month enrolment period) |
| **Patient follow-up** | 12 months |
| **Study aim** | Primary objective:  To evaluate the efficacy of a short, standardised spa therapy intervention on the return-to-work rates at 1 year for patients on sick leave due to lower back pain from 4 to 24 weeks’ duration.  Secondary objectives:  To evaluate the efficacy of a short, standardised spa therapy intervention on the pain, function, quality of life and number of days of sick leave at 1 year for patients on sick leave due to lower back pain from 4 to 24 weeks’ duration. |
| **Methodology** | A multi-centre, comparative, randomised, pragmatic trial using a modified ZELEN method. |
| **Number of sites** | 6 recruiting sites and 6 spa centres |
| **Number of patients** | 700, of whom:  - 350 in the intervention arm (standardised spa treatment)  - and 350 in the control arm (standard treatment) |
| **Selection criteria** | Inclusion criteria:   - Men or women aged from 18 to 60 years (inclusive); - Isolated lower back pain or back and radicular pain after classification of the disease (with the lower back numeric pain scale score being higher than the radicular numeric pain scale score); - Patients on sick leave due to common lower back pain from 4 to 24 weeks’ duration and for those in which an extended period of sick leave is expected; - Medical examination carried out in advance, the results of which will be communicated to the patient; - Patients having provided their written informed consent to take part in the study; - Patients affiliated with a social security scheme (beneficiary or entitled).   Exclusion criteria:   - Cognitive or behavioural difficulties making the assessment impossible; - Difficulties in comprehension and communication in the French language, making the assessment impossible; - Contraindication to undergo a short spa therapy programme. |
| **Study treatment** | Short, standardised spa therapy (5 days). |
| **Study progress** | One enrolment visit, followed by the intervention protocol for patients in the “standardised spa therapy” arm, then follow-up by mail at Month 3, 6 and 12.  D0 - Enrolment visit and randomisation   - Medical examination - Verification of eligibility criteria - Proposal of cohort study and collection of signed informed consent form - Enrolment - Patient contact information (name and surname, email, phone number) - Demographic information (age, sex) - Socioprofessional information (level of studies and profession) - Date sick leave started - Clinical information regarding lower back pain - Previous and ongoing treatment for lower back pain - Numeric pain scale - Quebec questionnaire - HAD questionnaire - Quality of Life, assessed with: MOS SF12 - FABQ questionnaire - CSQ questionnaire - Randomisation - Proposal of therapy for patients randomised into the intervention group and collection of signed informed consent form   Intervention protocol for patients randomised into the “spa therapy” arm   - Duration: five days, consisting of spa therapy sessions (exercises and hydrotherapy) and group therapy education   Assessments at Months 3, 6 and 12   - By post or email, together with a phone call if no response is received - Professional status/Return to work - Sick leave periods since the previous visit - Numeric pain scale - Lower back pain progress - Treatment since the previous visit - Adverse events collected - Quebec questionnaire - HAD questionnaire - MOS SF-12 questionnaire - FABQ questionnaire (only at the Month 12 assessment) - CSQ questionnaire (only at the Month 12 assessment) - Treatment satisfaction at 12 months   Pain assessment every fortnight  Numeric pain scale via telephone (IVR system) |
| **Primary and secondary**  **endpoints** | Primary endpoint  The primary endpoint will be the return-to-work rate at 1 year.  Secondary endpoints  The secondary endpoints will be as follows:   - Area under the curve of pain over the past 48 hours, assessed every fortnight by a numeric scale from 0 to 100 at 1 year - Functional assessment at 1 year (Quebec scale) - Quality of Life assessment at 1 year (MOS SF-12 questionnaire) - TWIST at 1 year (pain) - Number of days of sick leave between 6 months and 1 year after enrolment |
| **Statistical analysis** | An intention-to-treat analysis will be carried out with the data. The return-to-work rate percentage will be compared using the Chi-squared test. Area under the curve of pain and the TWIST will be compared using the Mann–Whitney U test. The other quantitative secondary endpoints will be compared using a linear mixed effects regression model.  The statistical analysis will be carried out at the [name] Epidemiology Centre - Hôtel Dieu, under the responsibility of [name] and [name]. SAS software will be used. |

# GENERAL OUTLINE OF THE STUDY

Management centre: elegibility criteria

**Enrolment visit**

Collection of ICF1 for participation in a cohort study lasting 1 year

**Randomisation**

Intervention arm

Standardised spa therapy

Control arm

Standard treatment

Collection of ICF2 for participation

Assessment at D0

**Local recruitment (local press**

**posters in pharmacies, doctors’ waiting**

**rooms) and at medical visits**

Assessment at D0

Intervention (spa therapy, group therapeutic education and back guide)

Follow-up at 3 months, 6 months and 1 year by post or email

+ numeric pain scale every fortnight by telephone

|  | **Enrolment visit + randomisation** | **Intervention**  **Visit** | **Visit 1**  **Mail/**  **phone** | **Visit 2**  **Mail/**  **phone** | **Visit 3**  **Mail/**  **phone** |
| --- | --- | --- | --- | --- | --- |
|  | D0 | M1-M3  Maximum after intervention | M3 | M6 | M12 |
| Inclusion and exclusion criteria | + |  |  |  |  |
| **Information and consent for the cohort study** | + |  |  |  |  |
| **Randomisation** | + |  |  |  |  |
| **Information and consent to participate in the therapy for patients randomised into the experimental arm** | + |  |  |  |  |
| **Patient contact information** | + |  |  |  |  |
| **Medical examination** | + |  |  |  |  |
| **Back guide and patient diary issued** | + |  |  |  |  |
| ASSESSMENT: | | | | | |
| - Socioprofessional information | + |  |  |  |  |
| - Clinical information regarding lower back pain | + |  | + | + | + |
| - Number of days of sick leave | + |  | + | + | + |
| - Return to work |  |  | + | + | + |
| - Number of periods of sick leave |  |  | + | + | + |
| - Treatments | + |  | + | + | + |
| - Numeric pain scale | + |  | + | + | + |
| - Quebec | + |  | + | + | + |
| - HAD | + |  | + | + | + |
| - MOS SF-12 | + |  | + | + | + |
| - FABQ | + |  |  |  | + |
| - CSQ | + |  |  |  | + |
| - Treatment satisfaction scale |  |  |  |  | + |
| **Adverse Events** |  | + | + | + | + |
| **INTERVENTION: Intensive spa therapy** |  | + |  |  |  |

# I - INTRODUCTION

## I - 1 - DATA FROM THE LITERATURE

Disability and sick leave related to lower back pain represent a major public health problem in developed countries (Andersson GB, Lancet 1999) and their costs to the healthcare system are comparable to those of heart disease, diabetes and depression (Druss BG, Am J Psychiatr 2000). The longer the sick leave lasts, the less likely it is that the patient will return to work (Waddell G, Occupational Medicine 2001). Extended periods of sick leave can reflect the level of complaints and functional incapacity, but being on sick leave could be an independent risk factor of extended sick leave. Factors such as professional experiences considered to be negative, low level of confidence in capacity to return to work and a low level of self-esteem have been identified as barriers for returning to work in this clinical situation (Magnuson L, Disab Rehabil 2007). Aside from the financial benefits, returning to work may also be a therapeutic improvement factor for lower back pain.

The rate of transition from acute lower back pain to chronic form is currently the subject of debate, as recent studies appear to contradict the previously stated rates of 8% to 10% with persistent pain as reported at 1 year in 47% in an Australian study (Menezes L, BMJ 2009) and 14% at 3 months in a French study (Coudeyre E, PloS ONE 2007). Subacute lower back pain (lasting between 4 and 12 weeks), however, is recognised as a preferred therapeutic target for preventing the transition to chronic form and the consequences this would have in terms of disability and treatment costs (Savigny P, BMJ 2009). Various interventions, which are often multidisciplinary, have shown an interest in reducing the intensity of the symptoms in this situation, but a significant number of patients have delayed symptoms and are on sick leave (Anema JR, Spine 2007).

Only one study has reported the progress of patients suffering from subacute lower back pain in France (Poiraudeau S, Rheumatol 2006). Around half of the patients were still symptomatic at 3 months, 41% of them had resorted to sick leave lasting an average of 30 days, and 20% had extended periods of sick leave. The non-return-to-work factors in subacute lower back pain have not been widely studied. A recent Norwegian study reported that the pain intensity at rest and at work and negative expectations related to return to work were non-return factors (Reme SE, BMC Musculoskeletal Dis 2009).

The most effective treatments for chronic lower back pain in terms of return to work are multidisciplinary programmes that combine physical activities with psycho-behavioural treatment (Schonstein E, Cochrane Database of Systematic Reviews 2003). However, most programmes proposed are intense (3 to 6 weeks) and are proposed at a late stage in cases of chronic lower back pain on extended sick leave (> 6 months). Some studies suggest, however, that less intense treatment proposed at an earlier stage could lead to a higher return-to-work rate than with standard care (Karjalaïnen JA, Cochrane Database of Systematic Reviews 2003, Anema JR, Spine 2007). There have been no therapeutic trials conducted on the subject in France and it is a known fact that the treatment and social protection system in this area has an influence on the return-to-work rate (Hanson, Spine 2000), which makes it difficult to generalise with regard to the results obtained in one health system or another.

## I - 2 - JUSTIFICATION OF THE RESEARCH

This is a multi-centre, randomised, pragmatic, intervention study comparing a short (5-day) standardised spa therapy combined with intensive rehabilitation and education in a spa therapy centre to the standard treatment for patients on sick leave from 4 to 24 weeks’ duration due to common lower back pain.

Why have we proposed such a study?

Patients on sick leave due to common lower back pain represent a significant healthcare cost, particularly in the patient group that does not return to work within 4 weeks, and that has a very high risk of chronic disorders. From a therapeutic perspective, too often, these patients undergo intensive treatment at too late a stage, with rather disappointing results from the long and costly treatment (the functional rehabilitation programmes offered to patients on extended sick leave in France lasted five weeks on average, most often in day admissions).

The hypothesis is that a short, more intense treatment at an earlier stage could have a beneficial effect in terms of recovery rates.

Why spa therapy?

In order to better respond to the public healthcare problems, spa centres aim to change the types of treatment offered by modernising them in two ways: by offering shorter, more intensive interventions, and including education (therapeutic education) in particular for patient populations which represent a problem in the therapeutic treatment and the treatment costs.

## I - 3 - EXPECTED RESULTS AND PROSPECTS

The study will be conducted in patients between the ages of 18 and 60 who have been on sick leave due to lower back pain for between 4 and 24 weeks.

Two groups will be studied in parallel: one will undertake a short (5-day) spa therapy intervention, during which they will receive a programme consisting of physical exercises, spa baths, psycho-behavioural treatment and therapeutic education. The other group (the control group) will receive standard care and advice typically given in these situations by general practitioners and specialists. Both groups will receive a guide on lower back pain.

While the efficacy of this programme has been demonstrated, it must be shown to lead to an increase in the return-to-work rates, improvement in pain and functional incapacity, and a quicker recovery. This would be the first treatment programme to demonstrate efficacy in this situation in France.

## I - 4 - Study feasibility

The main difficulties of this study were as follows:

- recruitment difficulties;

- follow-up difficulties.

In order to prevent these difficulties, four regions in France will be involved for this very common condition. All the research sites take part in general medical and specialist rheumatology networks in their respective regions. We also chose a local recruitment method with dissemination through the press, which proved to be effective, as well as recruitment through sick-leave agents from the Assistance Publique in these four regions, and employees from the Michelin group in the region of Auvergne.

Follow-up will be ensured by mail and by phone, in order to keep any missing data to a minimum.

Furthermore, the feasibility of the study is attested by:

- the experience of the clinical teams in the management and treatment of common lower back conditions, which will ensure sufficient recruitment;
- the experience of the methodologists in the planning and implementation of trials assessing non-pharmacological interventions;
- the experience of the spa therapy centres in the management of these patients.

## I - 5 - Expected benefits and risks

A short spa therapy programme, if shown to be effective, would allow the duration of sick leave to be reduced in patients with lower back pain.

There are no expected risks.

# II – STUDY OBJECTIVE

## II - 1 - PRIMARY OBJECTIVE

To evaluate the efficacy of a short, intensive and standardised spa therapy intervention on the return-to-work rates at 1 year for patients on sick leave from 4 to 24 weeks’ duration and for those in which an extended period of sick leave is expected.

## II - 2 - SECONDARY OBJECTIVES

To evaluate the efficacy of a short, intensive and standardised spa therapy intervention on the number of days of sick leave between 6 months and 1 year, as well as pain, function and quality of life at 1 year for patients on sick leave due to lower back pain from 4 to 24 weeks’ duration and for those in which an extended period of sick leave is expected.

# III – METHODOLOGY

## III - 1 - STUDY TYPE

This is a multi-centre, comparative, randomised, pragmatic, open trial using a modified ZELEN method.

## III - 2 - STUDY DURATION

The patients participating in this study will undergo 12 months of follow-up. The planned enrolment period is 24 months. The study is therefore expected to last 36 months. The patients will not be able to take part in a biomedical research study with therapeutic assessment likely to change the primary and secondary endpoints of the study for a duration of 12 months.

## III - 3 – RANDOMISATION ARM ASSIGNMENT

Randomisation will be stratified by site. The randomisation list will be prepared with variable block sizes. The list and block size will not be communicated to the investigators. The secrecy of the assignment will be upheld using a computerised randomisation system.

## III - 4 – EXPERIMENTAL DESIGN

**Randomised trial:**

Two patient groups will be studied: one group will be treated with a short, intensive and standardised spa therapy, and the other group will receive standard medical treatment.

The randomised, controlled trial is considered the gold standard for therapeutic assessment. Randomisation is the only method that allows comparable groups to be obtained for the known and unknown prognostic factors and screening bias to be limited.

The assessment of a spa therapy intervention raises specific methodological issues linked in particular to issues related to the choice of comparator and difficulties in achieving blinding (Boutron, JAMA 2004, Boutron, J Clin Epidemiol 2007). The planning, implementation, analysis and final written report of the results will also be done in accordance with the recommendations of the CONSORT Statement extension on non-pharmacological treatments (Boutron, Ann Inter Med 2008), and the CONSORT Statement extension on pragmatic trials (Zwarenstein M, BMJ, 2008).

**Choice of comparator**

This is a pragmatic study and, as such, the comparator will be the standard medical treatment of patients by their general practitioners, and specialists where necessary.

The content of this treatment will be systematically collected at the follow-up contacts at Months 3, 6 and 12.

**Justification of the modified Zelen method**

The primary endpoint is the return-to-work rate at 1 year. This criteria involves a certain level of subjectivity. Additionally, the secondary endpoints (pain, function and quality of life) are patient-reported criteria, which by definition are completely subjective. A recent study showed that, when there is no blinding, there is an overestimation of the treatment effect for randomised trials in which the endpoint is subjective (Wood L, BMJ 2008).

In this context, however, blinding of patients, therapists and evaluators is not possible. In order to limit the bias resulting from the lack of blinding, we propose to implement a modified Zelen method. First of all, all eligible patients will be invited to take part in a cohort study with the aim of assessing the return-to-work rate at 1 year, the duration of sick leave and the level of pain, incapacity and quality of life in patients with lower back pain. On a second occasion, after the randomisation stage, the patients randomised into the intervention group will be invited to take part in a study assessing the efficacy of a short, intensive and standardised spa therapy intervention. The patients willing to participate will sign a second consent form.

This method will prevent the risks of bias resulting from the lack of blinding. In a conventional randomised trial, the patients assigned to the control group (without intervention) are more likely to withdraw from the study, attempt to have the study treatment or change their behaviour during the endpoint assessment.

This scheme is acceptable in this context for several reasons:

1. With regard to ethics, the patients will be informed that, for scientific reasons, they will not be given details of any of the study hypotheses until the end of the study. This procedure of collecting the informed consent over two stages has already been used to assess rehabilitation, and several ethics committees have approved its use in this context (Quilty *et al.*, 2003, Rannou, National clinical research hospital protocol currently underway, Forestier R, ARD 2009).
2. With regard to methodology, the limitations of the Zelen method are the risk of contamination through refusal to undergo the intervention (short spa therapy programme). In the Thermarthrose study (Forestier R, ARD 2009), a large-scale, multi-centre trial assessed a specific treatment involving spa therapy vs standard treatment according to a Zelen method, with a 10% rate of contamination. The risk of contamination should be no higher in our study, taking into account:
   1. the lack of risk of the intervention;
   2. the lack of other treatments available;
   3. the duration of the intervention, which will be shorter;
   4. the patients who are on sick leave.

The risk of contamination in the standard-care group is highly unlikely, given that the short spa therapy programme is not currently offered outside this study.

Another risk of the Zelen method is the hypotheses being unblinded for patients. This risk is minimal, as the endpoint assessment visits (at M3, M6 and M12) will be done by post or email (or by phone, if no response is received), which prevents the patients from the two groups from being in contact with each other.

**Procedures for minimising missing data**

In order to minimise missing data, all patients will be contacted by phone and/or by email to remind them to send their assessment questionnaire in due course (3 months, 6 months and 12 months after enrolment) and, where necessary, they will be helped to fill in the questionnaire.

Furthermore, it has been demonstrated that offering clinical study patients a symbolic financial compensation improves response rates (Roberts PJ, Torgerson DJ, BMJ 2002). As such, at the end of the study, patients will receive a gift voucher when they have filled in and returned the questionnaires.

# IV – STUDY POPULATION

## IV - 1 - INCLUSION CRITERIA

- Men or women aged from 18 to 60 years (inclusive);
- Isolated lower back pain or back and radicular pain after classification of the disease (with the lower back numeric pain scale score being higher than the radicular numeric pain scale score);
- Patients on sick leave due to common lower back pain from 4 to 24 weeks’ duration and those in which an extended period of sick leave is expected;
- Medical examination carried out in advance, the results of which will be communicated to the patient;
- Patients having provided their written informed consent to take part in the study;
- Patients affiliated with a social security scheme (beneficiary or entitled).

## IV - 2 - EXCLUSION CRITERIA

- Cognitive or behavioural difficulties making the assessment impossible;
- Difficulties in comprehension and communication in the French language;
- Contraindication to undergo a short spa therapy.

## IV - 3 - REQUIRED NUMBER OF SUBJECTS

The return-to-work rate at 1 year is estimated to be 70% in the control group. The hypothesis is to reach 80% in the intervention group. With a 5% risk and a power of 80%, a total of 600 patients are planned to be enrolled: 300 patients in the short spa therapy group and 300 patients in the control group. Taking into account the risk of loss-to-follow-up, 700 patients will be enrolled.

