## IX -1- 5- Primary endpoint analysis

An intention-to-treat analysis will be carried out, i.e., all patients randomised will be analysed in their randomisation arm, regardless of the treatment received and any missing information. The bilateral tests will be carried out at the 5% threshold. The return-to-work rate percentage will be compared using the Chi-squared test.

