## IX - 4- CHOICE OF INDIVIDUALS TO BE INCLUDED IN THE ANALYSES

Adults (between the ages of 18 and 60), either male or female, with isolated or lower back pain or back and radicular pain after classification of the disease, on sick leave from 4 to 24 weeks, and who meet the inclusion criteria of the study.

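### IV-3 claims 80% power without allowing for spa refusal after randomisation, which the protocol accepts at up to 10%, and does not say whether the 80% rate already includes refusers

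*Protocol*

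**What the plan says.** **Sample size (IV-3).** "The return-to-work rate at 1 year is estimated to be 70% in the control group" and "The hypothesis is to reach 80% in the intervention group". Then: "With a 5% risk and a power of 80%, a total of 600 patients are planned to be enrolled", split equally at 300 per arm. Enrolment is raised to 700, and the only reason given is loss to follow-up.

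**Order of events (III-4, VII-1).** All patients sign a first consent form (ICF1) for a cohort study and are then randomised. Only those allocated to the spa are offered it, and those who accept sign a second form (ICF2).

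**Expected refusal (III-4, justification of the modified Zelen method).** The protocol names refusal of the spa as the way contamination arises. It cites an earlier multicentre spa trial in knee osteoarthritis, run "according to a Zelen method, with a 10% rate of contamination", and adds: "The risk of contamination should be no higher in our study". It regards contamination of the standard-care arm as highly unlikely.

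**Analysis (IX-1-5, IX-3, IX-4).** Under IX-1-5, "all patients randomised will be analysed in their randomisation arm", whatever treatment they received. The test is a chi-squared test, and "The bilateral tests will be carried out at the 5% threshold". IX-3 fills in missing primary outcomes by a maximum-bias rule. IX-4 describes the individuals to be analysed as adults with the condition "who meet the inclusion criteria of the study".

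**The concern.** Refusal comes after randomisation and can occur only in the spa arm. An as-randomised analysis keeps refusers in that arm although they have had standard care, so they pull its return-to-work rate towards the control rate. III-4 puts a ceiling on how often this will happen, but IV-3 does not carry the figure into the sample size. If the 80% describes patients who receive the spa, the analysis in IX-1-5 will not see a contrast of 70% v 80%, and the trial has less power than stated.

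There is also a smaller mismatch in the definition of who is analysed. IX-1-5 takes everyone randomised, while IX-4 takes those who meet the inclusion criteria. The two differ for any randomised patient later found ineligible.

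**Working it through.** **Inputs.** Control rate 70%, spa rate 80%, 300 per arm and 80% power (IV-3); two-sided 5% and chi-squared test (IX-1-5); refusal r between 0% and 10% (III-4); control-arm contamination taken as 0% (III-4). Assumptions not in the protocol: 80% is the rate among patients who take the spa, and refusers return to work at 70%.

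**Step 1: reproduce the stated size.** Pooled-variance formula without continuity correction:

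n per arm = [1.96·√(2·p̄·(1−p̄)) + 0.8416·√(p1(1−p1) + p2(1−p2))]² / (p2−p1)²

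With p1 = 0.70, p2 = 0.80 and p̄ = 0.75: [1.96·√0.375 + 0.8416·√0.37]² / 0.01 = (1.200 + 0.512)² / 0.01 ≈ 293.2, so 294 per arm or 588 in total. The protocol's 600 is this figure rounded up. Power at 300 per arm is 80.9%. The stated size is therefore correct for a contrast of 70% v 80% with nothing taken off for refusal.

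**Step 2: what the increase to 700 covers.** 1 − 600/700 = 14.3%. IV-3 assigns all of it to loss to follow-up.

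**Step 3: dilute the contrast.** As-randomised spa rate = 0.70 + 0.10·(1 − r).

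- r = 5%: 0.70 + 0.10·0.95 = 79.5%
- r = 10%: 0.70 + 0.10·0.90 = 79.0%

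**Step 4: power with complete outcomes.** Power = Φ{[(p2−p1)·√n − 1.96·√(2·p̄·(1−p̄))] / √(p1(1−p1) + p2(1−p2))}.

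For r = 10% and n = 300: (0.09·17.32 − 1.208) / 0.613 = 0.572, and Φ(0.572) = 71.6%.

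| Refusal | Contrast | Power, 300 per arm | Evaluable per arm for 80% power |
|---|---|---|---|
| 0% | 70% v 80% | 80.9% | 294 |
| 5% | 70% v 79.5% | 76.5% | 328 |
| 10% | 70% v 79% | 71.6% | 367 |

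Exact calculation for the Pearson test at 300 per arm gives 81.1%, 76.7% and 71.8%, so the approximation is adequate.

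**Step 5: does the attrition margin absorb the loss?** With all 350 per arm evaluable and 10% refusal, power is 78.1%. Restoring 80% would need 2 × 367 = 734 evaluable patients, more than the 700 to be enrolled.

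**Step 6: the other reading of 80%.** If 80% is the as-randomised rate and 10% refuse at the control rate, attenders would need (0.80 − 0.10·0.70) / 0.90 = 0.73 / 0.90 = 81.1%. Power is then as stated, and the hypothesis about the spa itself is slightly stronger.

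**Step 7: what these figures leave out.** Under IX-3, in the direction set against the spa, missing spa outcomes become failures and missing control outcomes become successes. At the implied 14.3% loss the expected rates are 0.80·0.857 = 68.6% in the spa arm and 0.70·0.857 + 0.143 = 74.3% in the control arm, before any refusal. The powers above therefore apply only to complete outcomes and must be labelled so.

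**The case against.** The strongest reply is that the 80% already includes refusers. IV-3 speaks of the rate reached in the intervention group. The trial is pragmatic, and IX-1-5 defines the groups as randomised. On that reading nothing is lost. This stands as a possible meaning, but IV-3 does not state it, and no figure elsewhere in the protocol settles it.

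Second, 10% is a ceiling. III-4 gives four reasons why refusal should be no higher here and gives no rate for this trial. That stands too: the supportable statement is a range from 72% to 81%. A reader might infer that the power simply is 72%, or that the sample-size arithmetic is wrong. The protocol supports neither, since the arithmetic reproduces.

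Third, refusers need not return to work at 70%. Worse outcomes would dilute the contrast further and better outcomes would dilute it less. The protocol gives no information on this.

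On the analysis set, a reader might infer that IX-4 would drop refusers from the spa arm alone, because one inclusion criterion is written consent to take part and refusers never sign ICF2. The text does not support that. Refusers sign ICF1 before randomisation. IX-4 mentions neither ICF2 nor acceptance of the spa. Reading the criterion as ICF2 would also remove every control patient. IX-1-5 expressly keeps everyone randomised. Nor can a direction of bias be given for such an exclusion, since refusers might do worse or better than others.

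**Conclusion.** The point holds in a limited form. The 80% power in IV-3 is right only if no one refuses the spa or if the 80% rate already includes refusers, and the protocol states neither. If 80% is the rate among attenders and refusers behave like controls, power at 300 per arm with complete outcomes lies between about 72% (10% refusal) and 81% (none). The shortfall is at most about 9 percentage points within the range the protocol accepts. The 700 enrolled would not close it at 10% refusal even with no loss to follow-up (78%).

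The mismatch between IX-4 and IX-1-5 is a conflict of wording only. It is not evidence of a plan to exclude refusers.

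**What to change.** **IV-3.** Adopt one of two statements.

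- If 80% is the rate among patients who take the spa: say that 300 per arm with complete outcomes gives about 81% power with no refusal, 77% at 5% and 72% at 10% (as-randomised contrast 70% v 79%), assuming refusers return to work at the control rate, and that these figures are before any imputation of missing outcomes under IX-3.
- If 80% is the as-randomised rate: say that it includes patients who decline the spa, and that attenders would then need about 81.1% at 10% refusal, on the same assumption about refusers.

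**IX-4.** Bring it into line with IX-1-5: the analysis includes all patients who signed ICF1 and were randomised, in their assigned arm, whether or not they signed ICF2.

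**Cost.** Wording only. There are no extra patients and no change of endpoint or test. The price is a less favourable power statement under the first option, or a slightly more demanding hypothesis under the second.
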